#### **3.3 Exploratory**

- 3.3.1 *Signals of improvement in food insecurity, nutrition insecurity, cost-coping behaviors, time demands, and financial well-being is defined by improvements in T4 (post intervention) measurements as compared to T1(baseline pre-intervention).*
- 3.3.2. *Adolescent and parent thoughts about MTM-Kids processes, the meals, and recommended improvements in the meals and study processes are defined as themes that emerge from analyses of qualitative interviews with the adolescents, and with their parents.*
-

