### **7.2.2 Surveys and Interview Questions for Parents**

Parents will be asked to complete established measures of household food and nutrition insecurity, time-demands, financial cost-coping behavior and financial wellbeing,

Household food insecurity will be measured by the 6-item Food Security Scale [53]. Parents will be asked to indicate whether they experienced the condition during the past 3 month and, in some cases, how often. Scores will be estimated by counting the number of affirmative responses (yes, sometimes, or often); these scores can be categorized, such that 0-1=very low food insecurity, 2-4= low food insecurity, and 5-6=high food insecurity. [53]

Household nutrition insecurity will be measured by the 4-item Nutrition Security Scale plus 2 items from the Healthfulness Choice Scale. [54] Parents will be asked to use a 5-point scale, anchored by 1=never and 5=always, plus a don't know/prefer not to answer option. Scores will be estimated by counting the number of affirmative responses (sometimes, often, or always); these scores can be categorized such that 0-

---

1=very low nutrition insecurity, 2-4= low nutrition insecurity, and 5-6=high nutrition insecurity. [54]

Parental role time-demands will be measured with a set of Patient-Reported Outcome Measurement System v.2 (PROMIS v.2) items that ask about satisfaction with perceived social role performance. [55] Parents will be asked to respond to the PROMIS items using a 5-point scale anchored by 1=not at all and 5=very much. Item responses will be summed and scored using the T-score metric. Higher scores indicate greater satisfaction with social role performance. [55]

Financial coping behaviors will be measured by 7 of the questions from the Financial Coping Behaviors Scale currently being asked in a study of financial distress during treatment of pediatric acute lymphoblastic leukemia (ALL; ACCL20N1CD). [56] Parents participating in MTM-Kids will only be asked about financial coping strategies with implications for the health of the adolescent or another family member. Parents will be asked to use a 3-point response scale anchored by 0=never and 2=several times) to indicate how often they used each coping behavior in the prior month. Item responses will be summed for a total score that can range from 0-14.[56]

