## 8 STATISTICS

We will calculate descriptive statistics (frequency, proportion, central tendency, range, standard deviation [SD], reliability) to describe the study sample and estimate proportions, odds ratio, and confidence intervals (CI) for a priori feasibility benchmarks (see Time & Events Table). Feasibility study data can provide unreliable effect size estimates given small sample sizes. [46, 58] Thus, we will follow Brown [59] and estimate SDs and CIs for signals of change in food-related insecurities, cost-coping, time demands and QOL and use upper limits of 80% CIs plus enrollment and retention data to estimate sample size for the future efficacy trial. We will also consider evidence for associations between improvement in food security and QOL from studies of MTM with adult populations in estimating sample size for the future trial. [11, 44] Within days of an interview, two coders per interview will use rapid qualitative content analysis to analyze verbatim transcripts, compare their results and engage in discussion to resolve any discrepancies. The conceptual model (Figure 1) will guide the rapid analysis.[60] The goal is to identify actions at multiple levels (meal, child, household, study) to inform refinements for validation testing and ultimately the protocol for the future trial. When all interviews have been completed, we will use traditional content analysis to identify themes in the data overall to inform further refinements.

To ensure a rigorous and reproducible study, we have taken the following steps:

- Established a plan to enroll a diverse sample
- Justified the sample size
- Selected established measures to measure study variables
- Established the data analysis plan prior to data acquisition
- Considered relevant biological variables

Because sex hormones can affect taste function, processing of sweet and bitter, and food acceptability, [61] we will enroll similar numbers of biological female and male adolescents for each aim and explore the role of biological sex in the quantitative and qualitative data about alterations in taste and meal acceptability.

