#### 15.2.2.2 *Nutrition Insecurity*

The following questions ask about your household's ability to decide what you eat

- 7. In the last 3 months, we had to eat foods that were not good for our health and well-being because we couldn't get other types of food
    - a. Never
    - b. Rarely
    - c. Sometimes
    - d. Often
    - e. Always
    - f. Don't know or prefer not to answer
  - 8. In the last 3 months, we know there were things we should or should not eat for our health and wellbeing, but we could not get healthful food.
    - a. Never
    - b. Rarely
    - c. Sometimes
    - d. Often
-

- e. Always
  - f. Don't know or prefer not to answer
9. In the last 3 months, we worried that the food we were able to eat would hurt our health.
- a. Never
  - b. Rarely
  - c. Sometimes
  - d. Often
  - e. Always
  - f. Don't know or prefer not to answer
10. In the last 3 months, we had to eat the same thing for several days because we didn't have money to buy other food.
- a. Never
  - b. Rarely
  - c. Sometimes
  - d. Often
  - e. Always
  - f. Don't know or prefer not to answer
11. In the last 3 months, we could control if we were able to eat quality food.
- a. Never
  - b. Rarely
  - c. Sometimes
  - d. Often
  - e. Always
  - f. Don't know or prefer not to answer
12. In the last 3 months, we could control if we were able to eat foods good for our health.
- a. Never
  - b. Rarely
  - c. Sometimes
  - d. Often
  - e. Always
  - f. Don't know or prefer not to answer

*15.2.2.3 Parent-Reported Acceptability, Appropriateness, Feasibility, Affordability, & Accessibility*

These questions ask your opinions about the Medically Tailored Meals for Kids (MTM-Kids) program. Please select the response that best fits your thoughts.

---

Please provide the following information for study-related communications

Mobile phone number (XXX) XXX -XXXX

Preferred contact method for study reminders and surveys (check one):

|              |       |
|--------------|-------|
| Mobile phone | Email |
|--------------|-------|

Best days of the week to contact you (check all that apply)

\_\_\_ Monday \_\_\_ Tuesday \_\_\_ Wednesday \_\_\_ Thursday \_\_\_ Friday \_\_\_ Saturday \_\_\_ Sunday

Best time(s) of day to reach you (check all that apply)

\_\_\_ Morning \_\_\_ Afternoon \_\_\_ Evening

Your home address

House number:

Street name:

City:

Zip code:

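### Nutrition insecurity is collected on 1-5 items but scored as a yes/no count cut at *sometimes*, so graded improvement on either side of the cut shows as no change from T1 to T4

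*Protocol*

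**What the plan says.** Section 7.2.2 builds the measure from two instruments: "Household nutrition insecurity will be measured by the 4-item Nutrition Security Scale plus 2 items from the Healthfulness Choice Scale". On the response format it says: "Parents will be asked to use a 5-point scale, anchored by 1=never and 5=always, plus a don't know/prefer not to answer option". The score is then a count that may be banded: "Scores will be estimated by counting the number of affirmative responses (sometimes, often, or always); these scores can be categorized such that 0" to "1=very low nutrition insecurity, 2-4= low nutrition insecurity, and 5-6=high nutrition insecurity" (the sentence runs over a page break). The measure and its bands are attributed to reference [54].

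The items are in Appendix II, 15.2.2.2. Items 7-10 describe insecurity, so a more frequent answer is worse; item 9, for example, reads: "In the last 3 months, we worried that the food we were able to eat would hurt our health". Items 11-12 ask about control over eating quality or healthy food, so a more frequent answer is better. No reverse coding is stated.

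Three places use the score. Section 3.3 says the exploratory signal "is defined by improvements in T4 (post intervention) measurements as compared to T1(baseline pre-intervention"). Section 8.3.3 reports mean total scores, ranges and SDs at T1 and T4. Section 8 plans SDs and CIs for change in food-related insecurities and will "use upper limits of 80% CIs plus enrollment and retention data to estimate sample size for the future efficacy trial".

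**The concern.** Three of the five answers share the code 1 and two share the code 0. A household can therefore report a clear change in frequency and keep the same score. Section 1.2 lists the sensitivity of the proposed pathways to the meals as something this study should clarify, and at most 15 parents will supply the data.

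Two things are at stake. The T1-T4 display could understate a partial improvement, which is a plausible result of 12 weeks of deliveries. And the SD of change carried into planning would belong to a coarser score than the one the form already collects.

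The protocol keeps graded answers for its other multi-level scales: taste alteration, symptoms, role satisfaction, financial coping, financial well-being and the acceptability domains. Food insecurity is also counted, but its items offer only yes/no or a few levels, so the 5-point nutrition items give up the most detail.

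**Working it through.** **Step 1: reproduce the stated range.** Score each item 1 if the response is 3 or higher and sum over six items. The range is 0 to 6, which matches the bands 0-1, 2-4 and 5-6.

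**Step 2: score the example.** Items 7-10 go from *always* (5) to *sometimes* (3); items 11-12 do not change.
- Sum of the responses to items 7-10: 4 × 5 = 20 falls to 4 × 3 = 12, an 8-point improvement on a possible range of 4-20.
- Count as written: 4 to 4 if both control items are *never*; 6 to 6 if both are *sometimes* or *always*. The change is 0 in each case.
- Reversing items 11-12 does not alter this, because they are unchanged in the example.

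**Step 3: count the hidden moves.** Each item has 10 possible improving moves between levels. Four leave the code unchanged: *always* to *often*, *always* to *sometimes*, *often* to *sometimes*, and *rarely* to *never*.

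**Step 4: direction of items 11-12 (a separate fault in the same rule).** As written, the best household (insecurity *never*, control *always*) scores 0 + 2 = 2. The worst (insecurity *always*, control *never*) scores 4 + 0 = 4. Both fall in the 2-4 band. If the household in step 2 also moved from *never* to *always* on control, its count would go from 4 to 6. Any rescoring has to settle this too.

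**Step 5: size of the loss.** The documents give no effect, SD or baseline distribution, so everything here is assumption. The model has six items coded in one direction. Item value = μ + 0.8 × trait + 0.6 × error, cut at -1.2, -0.4, 0.4 and 1.2. The trait correlates 0.6 between visits, half the error variance is shared across visits, and improvement is 0.5 on the unit-variance item scale. The baseline share at *sometimes* or worse is Φ(μ + 0.4). The standardised change is mean change / SD of change, and the sample-size ratio is (mean-score value / count value)².

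| μ | Baseline share affirmative | Standardised change, mean of 1-5 | Standardised change, count | Sample-size ratio |
|---|---|---|---|---|
| -0.8 | 34% | 0.589 | 0.492 | 1.43 |
| -0.4 | 50% | 0.624 | 0.541 | 1.33 |
| 0 | 66% | 0.637 | 0.544 | 1.37 |
| 0.4 | 79% | 0.640 | 0.508 | 1.59 |
| 0.8 | 88% | 0.627 | 0.440 | 2.03 |
| 1.2 | 95% | 0.601 | 0.360 | 2.79 |

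For the first row, (0.589 / 0.492)² = 1.43.

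**Step 6: sensitivity to the assumptions.**
- Improvement of 0.7 instead of 0.5: ratios of 1.36 to 2.78, essentially the same.
- Item locations spread from -1 to +1, so that items do not saturate together: about 1.3 at shares of 37-63%, 1.44 at 74%, 1.64 at 84% and 1.96 at about 90%.
- A different model (the four insecurity items only, correlation between visits 0.5, shared item variance 0.4 to 0.8): 1.30-1.42 at shares of 50-66%, 1.58-1.71 at 82%, 2.15-2.39 at 92% and 3.33-3.78 at 97%.

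The lower end is stable at about 1.3. The upper end depends on how close baseline answers lie to the ceiling and on how alike the items are.

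**The case against.** The strongest reply is that the count may be the published scoring of an established measure. The protocol attributes the measure and bands to [54], lists established measures among its rigor steps, and counts affirmative answers for food insecurity as well. That stands as a reason to keep the count in view. What [54] prescribes cannot be checked here, so the count should not be called a scoring error. It does not change the arithmetic in steps 2 and 3, and the protocol itself joins items from two scales into one count.

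A reader might infer that the study would miss a real effect, or that its power is much reduced. The documents do not support that. Objective 2.3.1 is descriptive, section 8.3.3 plans no test, and section 8.2.1 says the sample size does not rest on an effect size. Power figures would describe an analysis that nobody plans.

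A reader might also infer that enrolled households start near the top of the scale, where the loss is largest. Section 5.1 admits families on utility or transportation insecurity alone, and the hardship questions in the screener do not ask about diet quality. The large ratios are therefore possible but not established.

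The effect on the next trial is bounded too. Section 8 acknowledges that feasibility data give unreliable effect sizes, also draws on adult studies, and no primary outcome for that trial is named. The 1-5 answers are kept and could be rescored. Rescoring after seeing the data would, however, sit badly with the statement in section 8 that the analysis plan was set before data acquisition.

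**Conclusion.** The point holds as a modest one. The scoring rule in section 7.2.2 treats *sometimes*, *often* and *always* alike, and *never* and *rarely* alike. Improvement within either group gives exactly zero change in the T1-T4 signal and is absent from the SD of change. That much follows from the text alone.

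Its size rests on assumed latent-normal models with all items in one direction. The count needs about 1.3 to 1.6 times the sample of the item mean when roughly 35-80% of baseline answers are affirmative. It needs about 2 to 2.8 times only when nearly all are and the items behave alike; spreading the items brings the top of the range down to about 2.0. These ratios concern within-person change, so they are only a guide for the two-group trial envisaged in section 1.2. They also do not describe the score as written, because items 11-12 run the other way.

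The outcome is exploratory and descriptive, and the primary feasibility benchmarks are untouched.

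**What to change.** In sections 7.2.2 and 8.3.3:

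- Report the T1-T4 change and its SD on the mean of the 1-5 responses, with items 11-12 reverse-coded (6 minus the response) so that higher means more insecure. Use this SD where section 8 refers to planning the future trial.
- Treat don't know/prefer not to answer as missing, take the mean of the answered items, and state the minimum number of answered items in advance.
- Also show the four insecurity items and the two choice items separately, because they come from different scales.
- Keep the count and bands as a descriptive display for comparability, with items 11-12 reversed. State how *sometimes* is coded on those two items: reversing the 1-5 response before the cut and reversing the 0/1 code after it give different answers.

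The cost is a few lines of scoring text; no item, visit or burden is added. The downside is that the mean has no category labels and departs from the scoring the protocol attributes to [54]. The protocol should say so; the retained count supplies the labels and the comparability.

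### The nutrition-insecurity score counts two favourably worded items as insecurity, so the best-off and worst-off households land in the same category

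*Protocol*

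**What the plan says.** Protocol section 7.2.2 defines the instrument: "Household nutrition insecurity will be measured by the 4-item Nutrition Security Scale plus 2 items from the Healthfulness Choice Scale". All six items share one set of five replies, from never (1) to always (5), with an opt-out for parents who cannot or would rather not say. One scoring rule follows: "Scores will be estimated by counting the number of affirmative responses (sometimes, often, or always"). The resulting count is banded, the lowest band starting at 0: "1=very low nutrition insecurity, 2-4= low nutrition insecurity, and 5-6=high nutrition insecurity". Because the bands run up to 6, all six items must be in the count.

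Appendix 15.2.2.2 prints the items. Item 7 is typical of items 7 to 10: it asks how often the household ate unhealthy food for want of anything else. Items 11 and 12 run the other way: "In the last 3 months, we could control if we were able to eat quality food" and, in item 12, "we could control if we were able to eat foods good for our health". Neither section says that items 11 and 12 are reversed or scored apart.

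The score is used in three places:

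- Sections 2.3.1 and 3.3.1 name nutrition insecurity as an exploratory outcome, judged by improvement from T1 to T4.
- Section 8.3.3 reports mean total scores, ranges and SDs at both times.
- The opening of section 8 uses SDs and confidence intervals for change in food-related insecurities towards the sample size of the future trial.

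**The concern.** For items 7 to 10, a reply of sometimes or more often means the household is worse off. For items 11 and 12, the same reply means it is better off. Counting both as insecurity makes two of the six items work against the other four.

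The intervention delivers healthy meals, so control over eating quality and healthy food is something it could plausibly change. Gains on those items would then be recorded as losses. The observed T1-to-T4 signal would be biased, and the SD of change carried forward to the next trial would describe a score that mixes two directions. Section 8.3.4 applies the same analysis to the first 5 dyads, so the fault would also enter the review that precedes the validation test.

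**Working it through.** **Inputs.** Six items, scored 1 (never) to 5 (always). An item is affirmative if the reply is 3 or more (section 7.2.2). Bands are 0-1 very low, 2-4 low and 5-6 high (section 7.2.2). The direction of each item is read from Appendix 15.2.2.2.

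**Notation.** H is the number of affirmative replies on items 7-10 (0 to 4). C is the number of affirmative replies on items 11-12 (0 to 2).

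- Score as written: S = H + C, range 0 to 6. This reproduces the plan's range and bands.
- Score with items 11-12 reversed (never or rarely = 1 point): R = H + (2 − C), also range 0 to 6.

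**Answer patterns.**

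| Household | H | C | S as written | Band | R reversed | Band |
|---|---|---|---|---|---|---|
| Best-off: never on 7-10, always on 11-12 | 0 | 2 | 0 + 2 = 2 | low | 0 + 0 = 0 | very low |
| Worst-off: always on 7-10, never on 11-12 | 4 | 0 | 4 + 0 = 4 | low | 4 + 2 = 6 | high |
| No hardship, no control | 0 | 0 | 0 | very low | 2 | low |
| All hardship, full control | 4 | 2 | 6 | high | 4 | low |

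**Reach of the bands.** As written, a score of 5 or 6 needs H = 4 with C of at least 1, or H = 3 with C = 2. A household can be classed as high only if it affirms at least one control item. A household that affirms both control items scores at least 2 and can never be classed as very low.

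**Change from T1 to T4.**

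- As written: ΔS = ΔH + ΔC.
- Reversed: ΔR = ΔH − ΔC.
- Difference: ΔS − ΔR = 2ΔC.

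Each control item that moves from never or rarely to sometimes or more therefore shifts the recorded change by 2 points towards worsening.

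- Worst-off to best-off: ΔH = −4, ΔC = +2. ΔS = −4 + 2 = −2; ΔR = −4 − 2 = −6. The recorded fall is 2/6, one third, and the band does not change.
- Hardship unchanged, both control items gained: ΔH = 0, ΔC = +2. ΔS = +2; ΔR = −2. The sign is wrong.
- Control items already affirmative and staying so: ΔC = 0, so ΔS = ΔR. For example, always on 7-10 with sometimes on 11-12, moving to best-off, gives 6 to 2 as written and 4 to 0 reversed: 4 points either way.

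For the sample, the mean change as written equals the reversed mean change plus 2 × the mean of ΔC.

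**SD of change.** Var(ΔS) = Var(ΔH) + Var(ΔC) + 2Cov(ΔH, ΔC), and Var(ΔR) = Var(ΔH) + Var(ΔC) − 2Cov(ΔH, ΔC). If households whose hardship falls tend to gain control, the covariance is negative and the SD as written is too small. The protocol gives no figure for this covariance, so only its direction under that assumption can be stated.

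**The case against.** The strongest reply concerns weight, not correctness.

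- **Rank of the endpoint.** Nutrition insecurity is exploratory and analysed descriptively; no success benchmark in section 8.3.1 uses it. This stands.
- **Recoverability.** Items are recorded one by one, so the score can be recomputed after the last survey. This also stands, but only helps if someone notices that the written rule is wrong.
- **Categories are optional.** Section 7.2.2 says only that scores can be banded, and section 8.3.3 reports mean totals. On the raw count the two extremes still differ, 2 against 4, in the right order. That is true, but the raw mean carries the same fault, with bias 2 × the mean of ΔC.
- **One third is a single pattern.** It holds when all six items flip. Where the control items do not cross the threshold nothing is lost, and the protocol has no data on how often they will. This stands: the figure is an extreme-case illustration and not an expected attenuation. Likewise, the score rises only if the fall in hardship items is smaller than the gain in control items.
- **Future sample size.** Section 8 draws on several domains plus other evidence and does not single out this score. The effect there is possible but cannot be sized.
- **Left to a SAP.** Only the protocol was available, and a SAP might specify the reversal. But the protocol does not leave scoring open: it states a rule covering all six items, and that rule gives the wrong direction for two.

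**Conclusion.** The concern holds. Section 7.2.2 and Appendix 15.2.2.2 cannot both be followed and yield a valid insecurity score. As written, the best-off and worst-off households score 2 and 4 and share the low band; they should score 0 and 6, in the very low and high bands. The bias in any household's change is 2 points per control item that crosses the threshold, at most 4 points on a 0-6 scale. Its average size in this trial depends on how many households change on items 11 and 12, which the protocol does not say.

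This rests on reading items 11 and 12 as printed, with always as the favourable answer, and on all six items entering the count, which the 0-6 bands require. The primary feasibility conclusion is untouched. The affected results are the exploratory nutrition-insecurity signal and any use of its SD in planning.

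**What to change.** Amend the scoring sentence in section 7.2.2. Items 7-10 score 1 for sometimes, often or always. Items 11-12 score 1 for never or rarely. Sum the six. The score keeps its 0-6 range, so the existing bands can still be applied.

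The sentence should say explicitly how sometimes counts on items 11-12. Under the rule above it scores 0. Under a 6-minus-x reversal followed by the 3-or-more threshold it would score 1. The two versions differ only for that reply, so one must be named before analysis.

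The alternative is to report the four hardship items and the two control items as separate scores. It is equally sound but costs more: a 0-4 hardship score cannot reach the 5-6 band, so new cut-points would have to be defined.

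Either way, the scoring program used for the first 5 dyads and for the final analysis should follow the amended text. The first option costs one sentence, with no change to the questionnaire, visits or data collected.
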